## Introduction

Globally, tuberculosis (TB) is the leading cause of death among infectious diseases. Diabetes, human immunodeficiency virus infection, and malnutrition are recognized as major risk factors for developing active TB. According to the World Health Organization (WHO), achieving TB elimination by 2050 requires not only controlling active TB but also implementing treatment for latent TB infection (LTBI) [3]. LTBI is defined as infection with *Mycobacterium tuberculosis* in which a small number of viable bacilli persist in the host without being expelled externally; therefore, there is no transmission to others. Individuals are asymptomatic and have normal acid‑fast bacilli testing and chest radiography. Because residual bacilli cannot be directly detected, LTBI is diagnosed indirectly by measuring the host immune response to TB antigens. Individuals with LTBI are at risk of progressing to active TB disease, and multiple risk factors influence disease progression. Treating LTBI prevents progression to active TB at the individual level and reduces community transmission and overall TB prevalence [4,5].

According to the national TB surveillance data in the Republic of Korea, a total of 19,540 TB cases were notified in 2023, corresponding to an incidence rate of 38.2 per 100,000 population, representing a 9.2% decrease compared with 2022 [1]. Despite this continuous decline, the national TB burden in Korea remains disproportionately high relative to its socioeconomic status [2]. National policies for LTBI management are founded on cost‑effectiveness analyses, for which robust cohort data are essential. Korea has launched the “TB‑Free Korea” program to achieve TB elimination by 2030, with the goal of minimizing progression to active TB among persons with LTBI. To systematically implement LTBI policies, it is urgent to generate scientific evidence on the effectiveness and safety of TB preventive treatment (TPT). Furthermore, the factors associated with progression to active TB among individuals with positive LTBI testing have not been fully defined domestically.

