Building a prospective cohort to collect clinical information on LTBI‑positive individuals is needed to establish a research platform for answering these questions. In this manuscript, we provide an overview of the design, methods and scope of this cohort study. This Safety of Preventive Treatment in People at Risk for Tuberculosis (STEP-TB) study is supported by the Korea National Institute of Health as a national research project. The study findings and datasets will be used as scientific evidence for developing the national TB control master plan in accordance with the TB Prevention Act. We aim to provide evidence to inform national TB policy by evaluating the safety of TPT in the high‑risk groups for active TB disease.

Among the medical high-risk groups for TB, including individuals with chronic kidney disease (CKD), chronic lung disease, diabetes mellitus, malignancy, immunosuppressive conditions, and occupational exposure, the safety of TB preventive treatment remains an important clinical concern. CKD is of special interest because patients with CKD have an increased risk of TB and may be more vulnerable to drug-related adverse events. This study aims to evaluate the safety of TPT in individuals at high risk of developing active TB disease in Korea using a multicenter prospective cohort design. The primary objective is to specifically investigate whether CKD is associated with an increased risk of adverse events during TPT. The secondary objective is to assess the association between CKD and TPT completion, to describe the TPT cascade of care among individuals at high risk of TB, and to evaluate the preventive effectiveness of TPT in reducing progression to active TB during the follow-up period. These objectives will allow a comprehensive understanding of both the safety and effectiveness of TPT in high-risk populations.

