### Study population and analytic framework

After enrollment, all individuals referred for LTBI testing will constitute the source population of the cohort and will be described in terms of baseline characteristics (Table 2). Participants will then be followed according to their LTBI test results and subsequent treatment status (Fig 1). Individuals with negative LTBI test results will be followed to monitor progression to active TB. Among those with positive LTBI test results, participants will be categorized according to whether they receive TPT. Participants receiving TPT will be followed for both adverse events related to TPT and the development of active TB. Participants with positive test results who do not receive TPT will be followed to evaluate the incidence of active TB for comparative assessment.

**Table 2 pone.0350186.t002:** Study populations and outcomes in the cohort.

Study population	Description	Purpose of analysis	Outcomes assessed
All individuals referred for LTBI testing	High-risk population undergoing LTBI testing	Description of source population	Baseline characteristics
LTBI test negative	Participants with negative LTBI test results	Assessment of natural risk of TB among test-negative individuals	Incident active TB
LTBI test positive	Participants with positive LTBI test results	Population eligible for TPT	Stratified analyses according to TPT status
LTBI positive, TPT treated	Participants receiving tuberculosis preventive treatment	Primary safety analysis population	Adverse events related to TPT; Incident active TB
LTBI positive, TPT not treated	Participants with LTBI who do not receive TPT	Comparative assessment of TB risk	Incident active TB

LTBI, latent tuberculosis infection; TB, tuberculosis; TPT, tuberculosis preventive treatment

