### Outcome measures

The primary outcome is adverse events leading to permanent discontinuation of any drugs in the TPT regimen. This outcome will be defined as any clinical or laboratory event occurring during TPT that results in permanent discontinuation of one or more drugs in the prescribed regimen. For example, in patients receiving a 3HR regimen, discontinuation of rifampicin due to adverse events while continuing isoniazid to complete TPT will be considered as meeting the primary outcome.

The secondary outcomes are completion of TPT, the cascade of care for TPT, and the preventive effectiveness of TPT. TPT completion will be defined as completion of the prescribed TPT regimen within the recommended treatment period according to national guidelines. TPT cascade of care will be described by evaluating the proportions of individuals who are eligible for TPT, initiate treatment, and successfully complete treatment. The preventive effectiveness of TPT will be evaluated the incidence of progression to active TB during the follow-up period.

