### Statistical analysis

Baseline characteristics of participants undergoing LTBI testing will be summarized using means and standard deviations for normally distributed continuous variables, medians and interquartile ranges for non-normally distributed variables, and frequencies with percentages for categorical variables.

To investigate if the presence of CKD alters the risk of adverse events (present/absent) during TPT, logistic regression models will be built, initially categorizing CKD as a binary variable (present/absent) and then as a ternary variable (present severe, present and not severe, absent). The minimal sufficient adjustment set for inclusion in adjusted models will be derived from a directed acyclic graph (DAG). Potential effect modification by CKD treatment will be explored amongst individuals with CKD. All statistical analyses will be performed using R or SPSS software. Additional analyses will be considered further categorizing the outcome, e.g., on the basis of adverse event severity (ordinal logistic regression) or taking into account the association between an adverse event and the drugs in use. P-values will be corrected for multiple testing.

Assessment of the association between CKD and TPT completion will take place similarly, as will progression to active TB, albeit here using time-to-event models. Finally, the cascade of care analysis will be descriptive.

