### Sample size calculation

CKD was defined according to the Kidney Disease: Improving Global Outcomes (KDIGO) guidelines as an estimated glomerular filtration rate (eGFR) <60 mL/min/1.73 m² for at least 3 months or evidence of kidney damage.[7] This study will evaluate whether CKD, a major medical high-risk condition for TB, is associated with adverse events during TPT. It is anticipated that approximately 40% of individuals undergoing LTBI testing will be LTBI-positive and initiate TPT, of whom about 15% will have CKD. Assuming adverse event rates of 20% in the CKD group and 10% in the non-CKD group, a total of 548 TPT initiators will be required to detect this difference with a two-sided α of 0.05 and 80% power.

Based on an expected LTBI positivity rate of 40%, approximately 1,370 LTBI testing candidates need to be enrolled to yield a sufficient number of treatment initiators. This sample size will provide adequate statistical power to assess whether CKD is an independent risk factor for adverse events during TPT. A total target enrollment of 1,370 participants is planned, with competitive enrollment implemented across participating sites; per-site recruitment targets may be adjusted accordingly.

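### The cohort cannot support stable adjusted estimates for active TB or a conclusion on the preventive effectiveness of TPT; the TB analysis should be descriptive

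*Protocol article*

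**What the plan says.** The Introduction lists among the secondary aims "to evaluate the preventive effectiveness of TPT in reducing progression to active TB during the follow-up period". Outcome measures repeats this as a secondary outcome: "The preventive effectiveness of TPT will be evaluated the incidence of progression to active TB during the follow-up period". The section on study population and analytic framework names the comparison group: "Participants with positive test results who do not receive TPT will be followed to evaluate the incidence of active TB for comparative assessment".

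Statistical analysis first describes logistic models for CKD and adverse events, with CKD in two and then three categories and covariates chosen from a causal diagram. It then says that CKD and TPT completion will be handled in a similar way, "as will progression to active TB, albeit here using time-to-event models". Only the cascade of care is called descriptive.

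The sample size rests on adverse events alone: "a total of 548 TPT initiators will be required to detect this difference with a two-sided α of 0.05 and 80% power", and from that, "A total target enrollment of 1,370 participants is planned". Follow-up is 12 months from TPT initiation for treated participants and 12 months from baseline for the others, with a final-visit window of months 11 to 15 (Tables 3 and 4). No expected number of TB cases is given. The only TB rate in the document is the national figure, "an incidence rate of 38.2 per 100,000 population".

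**The concern.** A rare outcome, a cohort sized for a different endpoint and one year of follow-up are paired with a covariate-adjusted time-to-event analysis and a stated aim of evaluating effectiveness. With a handful of cases, an adjusted estimate depends heavily on one or two individuals and its interval is too wide to separate strong benefit from none.

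The Introduction says that the findings will serve as evidence for the national TB control plan. A null or erratic hazard ratio could be read there as evidence that TPT does or does not work in these patients.

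**Working it through.** **Inputs from the protocol article.** Enrolment 1,370; TPT initiators 548; LTBI positivity 40%; share positive and initiating TPT 40% (all Sample size calculation). Follow-up 12 months, final-visit window months 11 to 15 (Tables 3 and 4). National TB rate 38.2 per 100,000 per year (Introduction).

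**The plan's own figures.** 548 / 0.40 = 1,370, which reproduces. The 548 itself does not: the usual two-sided two-proportion formula (20% versus 10%, 15% with CKD) gives about 714. That is a separate matter. At 714 / 0.40 = 1,785 enrolled, TB cases would rise by about 30%, which changes nothing below.

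**Step 1: person-time.** 1,370 × 1 year = 1,370 person-years. If every final visit fell at month 15, 1,370 × 15/12 ≈ 1,710. The total could also be lower. People who finished TPT within the past two years may enrol, treated follow-up ends 12 months after TPT initiation, and only TB after enrolment counts.

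**Step 2: expected TB cases, all groups together (person-years × rate).**

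| Rate | 1,370 person-years | 1,710 person-years |
|---|---|---|
| 38.2 per 100,000 (document) | 0.52 | 0.65 |
| 10 times (assumed) | 5.2 | 6.5 |
| 25 times (assumed) | 13.1 | 16.3 |

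At the national rate the chance of no case at all in 1,370 person-years is exp(−0.52) ≈ 59%.

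**Step 3: who informs the TPT contrast.** 1,370 − 548 = 822 participants (60%) are expected to be test-negative. Among the 548 LTBI-positives, ignoring any treatment effect, the three rates give 548 × 0.000382 = 0.21, then 2.1 and 5.2 cases.

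**Step 4: the untreated comparators.** Expected positives: 0.40 × 1,370 = 548. Expected positive and treated: 0.40 × 1,370 = 548. The difference is 0.

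**Step 5: a more generous scenario (all inputs assumed).** Let 50% to 90% of the 548 positives be treated, the untreated rate r be 0.5% to 2% per year, and the hazard ratio be 0.4. Cases = U·r + T·r·0.4, with U untreated and T treated.
- Low end: 55 × 0.005 + 493 × 0.005 × 0.4 = 1.3.
- High end: 274 × 0.02 + 274 × 0.02 × 0.4 = 5.5 + 2.2 = 7.7.

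The Schoenfeld formula for 80% power at two-sided 0.05 is 7.849 / [p(1 − p)(ln HR)²], with p the treated share. For HR 0.4, (ln HR)² = 0.840. This needs 38 events at p = 0.5 and 104 at p = 0.9. Power over this range is about 5% to 25%. Getting 38 events would take an untreated rate of 38 / (274 + 274 × 0.4) = 9.9% per year, about 260 times the national rate. With a stronger assumed effect, HR 0.2, power is still only 6% to 54%.

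**Step 6: precision at the best corner of Step 5.** Rounded to 5 untreated and 2 treated cases, before any covariate adjustment, the standard error of the log rate ratio is √(1/5 + 1/2) = 0.837. The upper 95% limit is exp(2 × 1.96 × 0.837) ≈ 27 times the lower.

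**The case against.** The strongest reply is that the protocol does not clearly join the two things criticised. The sentence in Statistical analysis follows on from CKD and TPT completion, so the time-to-event model may be meant for CKD and not for TPT. Outcome measures ties effectiveness to incidence, and Table 2 lists incident active TB by group, so much of a descriptive analysis is already implied. This stands in part: the intended contrast is unclear. But the effectiveness aim is explicit, only the cascade is called descriptive, and the case numbers are too small for either contrast.

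A second reply is that the cohort is selected for TB risk, so the national rate is too low, and the multiples of 10 and 25 are assumptions. That is correct. It is why the working extends to 2% per year in untreated positives, and the conclusion does not change.

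A third reply is that this is a condensed article, that minimum event counts, penalisation and interval methods belong in a SAP, and that power is claimed only for adverse events. That is fair, and none of those absences is the point. The objective and the class of model are stated here, and those are what should change.

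Three stronger readings are tempting but unsupported:
- **That the models cannot be fitted.** A penalised model runs on a handful of events. The problem is instability and imprecision.
- **That a TB case count for CKD follows from the stated 15%.** That share belongs to TPT initiators, not to all enrolled, and the Discussion says that TB risk is markedly raised in CKD.
- **That 1,370 person-years is a ceiling.** The visit window allows about 1,710.

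**Conclusion.** The point holds. Across all groups, the design yields about 0.5 TB cases at the document's only rate, and about 5 and 13 at assumed multiples of 10 and 25. Among the LTBI-positive participants who inform the TPT contrast, the more generous assumptions give about 1 to 8 cases, against 38 to 104 needed for HR 0.4. The cohort's true TB rate is not in the document, so these counts are a range and not a forecast.

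The comparator problem needs no assumed rate: the sample size text, taken at its word, leaves no untreated LTBI-positive group. A reader might infer that the protocol claims power for TB, or that the time-to-event model is certainly the effectiveness analysis. It does neither. The supportable conclusion is that neither stable adjusted estimates nor a statement on preventive effectiveness can come from this design. The primary safety analysis is untouched.

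**What to change.** - **Statistical analysis:** make the TB analysis descriptive. Report incidence per 1,000 person-years with exact Poisson 95% intervals for each Table 2 group. If a model is kept, state whether it addresses TPT or CKD, label it exploratory, limit its covariates to what the event count allows, and use a penalised (Firth) fit because events are sparse.
- **Introduction and Outcome measures:** replace the aim of evaluating preventive effectiveness with describing the incidence of active TB by TPT status.
- **Sample size calculation:** separate LTBI positivity from the share of positives who start TPT, so that the expected number of untreated positives is visible.

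These are changes of wording and analysis and need no extra participants. The cost is a more modest secondary claim.

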### Sample size calculation

CKD was defined according to the Kidney Disease: Improving Global Outcomes (KDIGO) guidelines as an estimated glomerular filtration rate (eGFR) <60 mL/min/1.73 m² for at least 3 months or evidence of kidney damage.[7] This study will evaluate whether CKD, a major medical high-risk condition for TB, is associated with adverse events during TPT. It is anticipated that approximately 40% of individuals undergoing LTBI testing will be LTBI-positive and initiate TPT, of whom about 15% will have CKD. Assuming adverse event rates of 20% in the CKD group and 10% in the non-CKD group, a total of 548 TPT initiators will be required to detect this difference with a two-sided α of 0.05 and 80% power.

Based on an expected LTBI positivity rate of 40%, approximately 1,370 LTBI testing candidates need to be enrolled to yield a sufficient number of treatment initiators. This sample size will provide adequate statistical power to assess whether CKD is an independent risk factor for adverse events during TPT. A total target enrollment of 1,370 participants is planned, with competitive enrollment implemented across participating sites; per-site recruitment targets may be adjusted accordingly.

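### With the protocol's own inputs, 548 TPT initiators give about 70% power for the CKD comparison, not the stated 80%

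*Protocol article*

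**What the plan says.** The section Sample size calculation gives all the inputs for a two-group comparison of proportions:

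- Rates: "Assuming adverse event rates of 20% in the CKD group and 10% in the non-CKD group".
- Share with CKD among those starting treatment: "of whom about 15% will have CKD".
- Result, with its error rates: "a total of 548 TPT initiators will be required to detect this difference with a two-sided α of 0.05 and 80% power".
- Yield: "approximately 40% of individuals undergoing LTBI testing will be LTBI-positive and initiate TPT", from which the enrolment target of 1,370 follows.

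The section names no formula or software and no allowance for loss. It then concludes: "This sample size will provide adequate statistical power to assess whether CKD is an independent risk factor for adverse events during TPT". The Statistical analysis section plans logistic regression with CKD first as a binary factor, adjusted for a set derived from a directed acyclic graph. It adds: "P-values will be corrected for multiple testing".

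**The concern.** A comparison split 15:85 is much less efficient than a balanced one, because the smaller group dominates the standard error. Here only about 82 people carry the CKD side of the primary comparison, and 548 looks too small for the stated power at that split.

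Whether CKD raises the risk of adverse events is the primary objective in the Introduction, and the results are meant to inform national tuberculosis policy. If the real power is nearer 70%, a doubling of risk from 10% to 20% would be missed about three times in ten, rather than two in ten as stated. In a safety study, a non-significant result described as adequately powered could be taken as reassurance that it does not provide.

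**Working it through.** **Inputs**, all from Sample size calculation: p1 = 0.20 (CKD), p2 = 0.10 (no CKD), CKD share 0.15, two-sided alpha 0.05 (z = 1.960), target power 80% (z = 0.842), N = 548, yield 0.40.

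**Step 1. The plan's own figures.** 548 / 0.40 = 1,370, so the enrolment step is correct and contains no allowance for loss. The figure to test is 548.

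**Step 2. Group sizes.** 0.15 × 548 = 82.2, so n1 = 82 and n2 = 466.

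**Step 3. Power at 548** (pooled two-proportion test).

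- Pooled rate: (82 × 0.20 + 466 × 0.10) / 548 = 0.115.
- Standard error under the null: √[0.115 × 0.885 × (1/82 + 1/466)] = 0.0382.
- Standard error under the alternative: √[0.16/82 + 0.09/466] = 0.0463.
- Power = Φ[(0.10 − 1.960 × 0.0382) / 0.0463] = Φ(0.543) = 70.6%.

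Exact enumeration of the Pearson test over all outcomes at 82 versus 466 gives 70.3%.

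**Step 4. N for 80% power at 15:85.**

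N = [1.960 × √(0.115 × 0.885 / (0.15 × 0.85)) + 0.842 × √(0.16/0.15 + 0.09/0.85)]² / 0.10²
= [1.960 × 0.8934 + 0.842 × 1.0828]² / 0.01 = 708.9, that is 709.

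Rounding up within each group gives 714. At the 40% yield, 709 / 0.40 = 1,772.5, about 1,773 enrolled.

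**Step 5. Does another two-sided method give 548?**

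| Method (two-sided 0.05) | N for 80% at 15:85 | Power at 82 vs 466 |
|---|---|---|
| Pooled normal | 709–714 | 70.6% |
| Exact Pearson | – | 70.3% |
| Continuity-corrected (Yates) | 787 | 64.8% |
| Exact likelihood ratio | – | 66.9% |
| Fisher | – | 66.2% |
| Arcsine | 764 | 66% |
| Wald, log odds ratio | 653 | 72.7% |
| Wald, log risk ratio | 609 | – |
| Unpooled normal | 920 | 58% |
| Unpooled, rates swapped between groups | 619 | – |

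A 1:1 split gives 398, or 438 with continuity correction. None of these is within 3% of 548, and none of the powers is within 2 points of 80%.

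**Step 6. What 548 does deliver.**

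- At 82 versus 466 and a 10% rate without CKD, power reaches 80% when the CKD rate is about 21.5% (pooled formula; odds ratio (0.215/0.785)/(0.10/0.90) ≈ 2.5, against 2.25 for 20% versus 10%).
- At 20% versus 10%, 548 reaches 80% with about 118 CKD initiators: 118/548 = 21.5%.

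**The case against.** **The CKD share is only approximate.** The protocol says about 15%, so the split could be somewhat kinder. At 17% the power is 74% and at 18% it is 76%; 80% needs 21 to 22%. That is about 118 CKD initiators instead of 82, over 40% more, which is further than an approximate 15% can reasonably stretch.

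**The test may have been one-sided.** A one-sided 0.05 test gives 78.9% power at 548, close to the stated figure. It needs 567 to 574 initiators for 80%, so it still does not reproduce 548, and the text says two-sided.

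**The shortfall is modest.** This is an observational cohort that will report estimates from regression models. The power gap is about 10 points, and the detectable CKD rate moves only from 20% to about 21.5%. This stands: it argues for a corrected sentence rather than a redesign.

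A reader might also infer more than the document supports:

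- *That covariate adjustment must lower power further.* The calculation is unadjusted while the claim concerns an independent risk factor, but the direction of the effect is not known. With an assumed R² of 0.1 to 0.3 between CKD and the covariates, power falls to about 67% to 57%. Adjustment for prognostic covariates can work the other way: in simulation with a covariate unrelated to CKD and an assumed log odds ratio of 1.0 or 1.5 per SD, likelihood-ratio power rose from 67% to 72% or 77%. The net effect depends on an adjustment set that the article does not list.
- *That the multiplicity correction contradicts the 0.05 used.* The correction sentence follows the one on additional analyses, and the Introduction names one primary objective. Which tests it covers is ordinarily settled in the analysis plan, which is not shown.
- *That 548 came from an equal-allocation calculation inflated for loss* (438 / 0.8 = 547.5). This is conjecture: the section states no 20% loss allowance. The shortfall does not depend on where 548 came from.
- *That the miss rate is at least 30%.* It is about 30%: 29.4% by the pooled formula and 29.7% by exact enumeration.

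**Conclusion.** The point holds for the stated power. On the protocol's own inputs, 548 TPT initiators give about 70% unadjusted power (58% to 73% across the two-sided methods tried), not 80%. At a 15% CKD share, 80% needs about 709 initiators and about 1,773 enrolled, which is 161 initiators and 403 participants more than planned.

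This rests only on figures printed in Sample size calculation and on a standard two-sided comparison of two proportions. It makes no assumption about adjustment, loss to follow-up or multiplicity. The document does not establish that adjustment or the planned P-value correction takes the primary test below 70%. What can be said is that the calculation allows for neither, so its result cannot be carried over unqualified to the claim about an independent risk factor.

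**What to change.** Restate the power in Sample size calculation, for example:

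*With 548 TPT initiators, of whom about 82 have CKD, the unadjusted power to detect 20% versus 10% at two-sided 0.05 is about 70%; 80% power is reached for about 21.5% versus 10%. The calculation is unadjusted and makes no allowance for any multiplicity correction.*

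Amend the following claim of adequate power for an independent risk factor to agree with this, and name the formula used. The cost is a change of wording and a less favourable stated power; enrolment need not change.

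If the sponsor prefers to keep 80%, the arithmetic points to about 709 initiators (about 1,773 enrolled). Steering enrolment towards about 118 CKD initiators within the 548 would also reach it on paper. That is a trade-off rather than a free correction: it would alter the case mix of a cohort meant to describe routine care, and nothing in the protocol shows that so many CKD initiators can be recruited.

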In clinical practice, concerns about adverse events often lead clinicians to defer TB preventive treatment [20], even after LTBI is diagnosed, particularly in patients with complex comorbidities. This reflects a persistent lack of condition-specific safety data for LTBI treatment. While randomized controlled trials provide rigorous safety assessments, such as RIFAKiD-TB trial [21], their restricted eligibility and controlled settings may limit generalizability to real-world practice. As a prospective observational cohort, STEP-TB complements existing evidence by including diverse high-risk populations and capturing both anticipated and unanticipated adverse events under routine clinical care. The resulting real-world safety data can inform condition-specific risk assessment, support shared decision-making, and provide essential evidence for the safe expansion of LTBI preventive treatment strategies. The availability of condition-specific, real-world safety data may also enhance patient-centered care by enabling clearer, evidence-based communication about the risks and benefits of TPT for individuals undergoing or considered for LTBI testing.

In conlcusion, The STEP-TB study is a multicenter prospective observational cohort designed to generate real-world evidence on the safety and implementation of TPT in individuals at high risk of developing active TB. By systematically evaluating adverse events, treatment initiation, and completion across diverse high-risk populations, this study aims to inform clinical practice, patient-centered decision-making, and national TB control policies, thereby supporting the safe expansion of LTBI treatment strategies and contributing to TB elimination efforts in Korea.

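### The sample size section uses one 40% both as the LTBI positivity rate and as the rate of being positive and starting TPT, so the 1,370 target has no separate allowance for non-initiation

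*Protocol article*

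**What the plan says.** All the planning figures are in the Sample size calculation section of the protocol article.

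- On yield, it anticipates that "approximately 40% of individuals undergoing LTBI testing will be LTBI-positive and initiate TPT". It puts the CKD share of these initiators at about 15%.
- On the primary comparison, it takes event rates of 20% with CKD and 10% without, and concludes that "a total of 548 TPT initiators will be required to detect this difference with a two-sided α of 0.05 and 80% power".
- On enrolment, the next paragraph says: "Based on an expected LTBI positivity rate of 40%, approximately 1,370 LTBI testing candidates need to be enrolled". It fixes 1,370 as the total target, with competitive enrolment across sites.

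Other sections bear on whether every positive participant will start treatment:

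- Table 2 (Study population and analytic framework) defines a group described as "Participants with LTBI who do not receive TPT", to be followed for comparison of TB risk. Table 4 gives this group a visit schedule.
- The Abstract lists predictors of non-initiation among the secondary outcomes. Outcome measures includes the cascade from eligibility through initiation to completion.
- The Discussion says that "concerns about adverse events often lead clinicians to defer TB preventive treatment", particularly in patients with complex comorbidities.

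The article gives no initiation rate among LTBI-positive participants and no expected size for the untreated positive group.

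**The concern.** Positivity and the joint rate of positivity and initiation differ by a factor: the share of positives who start TPT. Giving both the value 40% sets that factor to 100%. The rest of the protocol assumes it is lower, since an untreated positive group and an analysis of non-initiation need people who do not start.

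Recruitment is counted in people enrolled, but the primary CKD comparison depends on the number who start TPT. If 40% is positivity, enrolment could close at 1,370 with fewer than 548 initiators and proportionally fewer with CKD, while the text still claims adequate power. If 40% is the joint rate, the positivity figure behind the target is misstated, and so is the implied size of the untreated positive group.

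**Working it through.** **Inputs from the Sample size calculation section.** 40% (both labels); 548 initiators; 15% CKD; event rates 20% (CKD) and 10% (non-CKD); two-sided alpha 0.05; 1,370 enrolled. **Assumed input.** Initiation among positives, *u*, is not given, so I show 90, 80, 70 and 60%.

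**Step 1: reproduce the target.** 548 / 0.40 = 1,370.0, and 1,370 × 0.40 = 548.0. The stated figure reproduces exactly, with no further factor.

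**Step 2: baseline power at 548.** For n1 CKD and n2 non-CKD initiators, with pooled rate p = 0.15 × 0.20 + 0.85 × 0.10 = 0.115:

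power = Φ{ [0.10 − 1.96 × √(p(1−p)(1/n1 + 1/n2))] / √(0.20×0.80/n1 + 0.10×0.90/n2) }

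At 548, n1 = 0.15 × 548 = 82.2 and n2 = 465.8. The null standard error is 0.0382 and the alternative standard error is 0.0463. So (0.10 − 1.96 × 0.0382) / 0.0463 ≈ 0.54, and power is about 71%. The shortfall from 80% comes from the 548 itself, which its own inputs do not reproduce (about 710 by the same pooled formula). That is a separate error; 71% is the right baseline here.

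**Step 3: 40% read as positivity.** Positives = 1,370 × 0.40 = 548. Initiators = 548*u*; untreated positives = 548(1 − *u*); CKD initiators = 0.15 × 548*u*; enrolment needed for 548 initiators = 548 / (0.40*u*), rounded up.

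| Initiation *u* (assumed) | Initiators | With CKD | Untreated positives | Power | Change from 71% baseline | Enrolment for 548 |
|---|---|---|---|---|---|---|
| 100% | 548 | 82 | 0 | 71% | none | 1,370 |
| 90% | 493 | 74 | 55 | 67% | −4 points | 1,523 |
| 80% | 438 | 66 | 110 | 62% | −8 points | 1,713 |
| 70% | 384 | 58 | 164 | 58% | −13 points | 1,958 |
| 60% | 329 | 49 | 219 | 52% | −18 points | 2,284 |

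**Step 4: 40% read as the joint rate.** Initiators = 548 whatever *u* is. Positivity must be 0.40 / *u*, and untreated positives = 1,370 × 0.40 / *u* − 548.

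| Initiation *u* (assumed) | Positivity required | Untreated positives |
|---|---|---|
| 90% | 44% | 61 |
| 80% | 50% | 137 |
| 70% | 57% | 235 |
| 60% | 67% | 365 |

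For any *u* below 100%, Step 3 contradicts the first sentence and Step 4 contradicts the second.

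**The case against.** A reader might infer that 1,370 cannot yield 548 initiators and also leaves no untreated comparison group. The documents do not support that, for three reasons.

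- The first sentence can be read as a joint rate. On that reading 1,370 gives exactly 548, untreated positives exist, and the fault is a wrong label in the next paragraph.
- The two consequences are alternatives. With full initiation the yield is 548 and the untreated group is empty. With any non-initiation at 40% positivity, the yield falls short but the group is not empty.
- Study population and Table 1 also admit people already on TPT, or who completed it within two years. The treated share of enrolees is therefore not capped at positivity times initiation among newly tested people. The stated derivation does not use these routes, since it counts testing candidates, but they rule out a flat impossibility.

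Three further points stand. Both 40% figures are approximate: at 95% initiation the joint rate is 38%, and 1,370 gives about 521 initiators, so rounding could cover a small amount of non-initiation. The 60 to 90% range has no anchor in the protocol, and the Discussion's remark on deferral is qualitative. The untreated group serves a secondary outcome for which no power is claimed.

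A reader might also fault the lack of an allowance for withdrawal. That is weak: Study procedures keeps participants who discontinue in the analysis with their available data, and a condensed article may leave an inflation factor to the full protocol.

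The inconsistency survives all of this: two different quantities share one value, and the protocol elsewhere assumes they differ.

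**Conclusion.** Wrong as written. The two uses of 40% agree only under complete initiation, which conflicts with the planned untreated group, the non-initiation and cascade outcomes, and the protocol's own account of deferral. The article does not settle which meaning is intended, so the size of the problem depends on the reading. If 40% is positivity, the loss is about 4 to 18 points of power below the 71% baseline across the assumed 90 to 60% initiation. If it is the joint rate, there is no loss of initiators from this source, but the stated positivity is too low. The figures assume a 15% CKD share, the stated event rates, the pooled two-proportion test without covariate adjustment, and no contribution from people enrolled already on or after TPT. The full distance from 80% power should not be charged to this point.

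**What to change.** - Reconcile the two sentences by saying which quantity the 40% is.
- State positivity, initiation among positives and CKD share as separate planning values, with any expected contribution from people enrolled already on TPT or after completing it.
- Restate, for 1,370 enrolled, the expected numbers of initiators, CKD initiators and untreated positives, and the resulting power.
- During competitive enrolment, track TPT initiators and CKD initiators across sites as the recruitment goal, alongside total enrolled.

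The cost is protocol wording and two tracked counts. Correcting the statement needs no extra participants, but the stated yield and power may become less favourable. If the sponsor then wants to guarantee 548 initiators, enrolment may have to exceed 1,370, which is a separate decision.
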